### Interventions

2.11

#### Low-level laser therapy protocol

2.11.1

The same device (Laser DMC therapy EC) will be used for both groups. During sham treatment, however, the device will emit a guide light and sound, but no energy. Sessions will be held twice a week for six weeks (total: 12 session) using the parameters listed in Table 1. The participant will be seated comfortably in a quiet room with no sound interference. The tip of the laser will be covered in plastic wrap to avoid cross-contamination and for purposes of hygiene. The skin at the irradiation sites will be cleaned with gauze soaked in 70% alcohol.

**Table 1 T1:**
[figure not shown]
Parameters.

A potentiometer will be used to measure the mean power of the equipment and therapeutic dose, ensuring safety to the participant and operator. Following the protocol suggested by Venezian et al^[13]^ and Carvalho et al.^[15]^(Fig. 2).

**Figure 2 F2:**
[figure not shown]
Acupuncture points will be irradiated - IG-4 (hegu) – On the radial side, between the 1st and 2nd metacarpal bone. This point exerts a strong, direct influence on the face, eyes, ears, nose and mouth. It is also used to calm the mind and alleviate anxiety.F-3 (taichong) – In the depression between the 1st and 2nd metatarsals near the metatarsal bases. Exerts a deep calming effect on the mind. Its calming action is enhanced when combined with IG-4. VB-34 (yanglingquan) – In the anterior and inferior depression of the head of the fibula. This is an important point to relax the tendons whenever there are muscle contractions. E-36(zusanli) – 3 cm below the patella and 0.5 cm to the side of the anterior edge of the tibia. Indicated for treating irritability, depression, insomnia, tiredness, fatigue and headache. ID-19 (tinggong) – In a depression anterior to the ear above the tragus. Indicated for treating problems in the ear region and temporomandibular joint dysfunction. BP-6 (sanyinjiao) – 3 cm above the prominence of the medial malleolus on the posteromedial border of the tibia. This is one of the most important points with a broad spectrum of action; exerts a strong calming effect on the mind and is generally used to treat insomnia.

### Statistical analysis

2.12

The data will be tabulated and treated using GraphPad PRISM version 7.0. The Kolmogorov-Smirnov test will be used to determine the normality of the data. Variables that fit the Gaussian curve will be expressed as mean and standard deviation. The ANOVA two-way will be used for comparisons between the groups, with the significance level set to 5% (*P* < .05). by one of the authors ([name], Applied Statistics Specialist).

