**Methods::**

A randomized, controlled, clinical trial will be conducted. Individuals 4 to 17 years of age with a diagnosis of DS and possible sleep bruxism will be screened at the Integrated Health Clinic of Nove de Julho University. We will evaluate orofacial dysfunction (Nordic Orofacial Test - Screening questionnaire), Masseter muscle activity during sleep will be assessed by BiteStrip and the masticatory muscles will be evaluated by electromyography (BTS TMJOINT) head posture as well as salivary cortisol and dopamine. After the evaluations, the participants will be randomized into 2 groups: Grupo 1 – treatment with low-level laser therapy at a wavelength of 808 nm; Group 2 – sham treatment (simulated laser therapy). Treatment will be conducted twice per week for a total of 12 sessions. The data will be tabulated and treated using GraphPad Prism version 7.0. The Kolmogorov-Smirnov test will be used to determine the normality of the data. Variables that fit the Gaussian curve will be expressed as mean and standard deviation. The ANOVA 2-way will be used for comparisons between the groups, with the significance level set to 5% (*P* < .05).

**ClinicalTrials registration number:** NCT04211870.

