There are limited studies related to disease management in children. Treatment involves the control of anxiety and sleep, psychotherapy, physical therapy, and medications. Considering the high prevalence and difficulty in resolving this condition due to the lack of established treatment, any knowledge about bruxism is important and can assist in establishing better assessment and treatment strategies. The goal of treatment is to reduce physical, muscular and psychological tension. Therefore, a multidisciplinary approach involving physical therapy, pharmacotherapy, dentistry and psychology is required.^[8,9]^

Acupuncture has also been successfully used for the treatment of bruxism, achieving a reduction in the activity of the masseter and anterior temporal muscles as well as a reduction of anxiety.^[10]^ The stimulation of particular acupoints can promote muscle relaxation, thereby alleviating muscle spasms, inflammation and pain. Moreover, such stimulation leads to the release of hormones, such as cortisol and endorphins, thereby promoting an analgesic effect.^[11]^ Acupuncture point stimulation can be achieved with the use of needles, laser or electric current.^[12]^

Low Intensity Laser Therapy is a noninvasive and inexpensive treatment. Trigger point irradiation is an effective treatment for orofacial pain as well as reduction of swelling and hyperemia.^[13]^ However, there are no studies reporting the result of applying low intensity laser therapy on acupoints in children with DS and bruxism.

The aim of the proposed study is to analyze salivary levels of dopamine and cortisol and muscle activity before and after treatment with low-level laser therapy administered to acupoints in children with DS.

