#### Inclusion criteria

2.3.1

(1)Children and adolescents with a diagnosis of DS(2)Four to seventeenyears of age(3)Bruxism, based on parental reports of the occurrence of grinding the teeth, incisal and/or occlusal and the questionnaire for the evaluation of bruxism

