### Evaluations

2.4

All evaluations will be performed before starting the treatment protocol and at the last session.

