### Allocation

2.10

The participants will be randomized to two groups with the aid of a randomization site (randomization.com): Group A – active photobiomodulation(n = 15); Group B – sham photobiomodulation(n = 15).

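### The two-way ANOVA in section 2.12 leaves open which term tests treatment; baseline-adjusted ANCOVA removes the ambiguity and, at assumed correlations of 0.3 to 0.7, matches or beats every valid reading

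*Protocol article*

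**What the plan says.** Section 2.12 (Statistical analysis) gives a single between-group test: "The ANOVA two-way will be used for comparisons between the groups", at the 5% level. The abstract repeats it. The only other test named is a Kolmogorov-Smirnov check of normality.

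The layout has to be put together from other sections:

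- Section 2.4 (Evaluations) sets two measurement times: "All evaluations will be performed before starting the treatment protocol and at the last session".
- The Introduction gives the aim as to "analyze salivary levels of dopamine and cortisol and muscle activity before and after treatment with low-level laser therapy".
- Section 2.10 (Allocation) gives the arms: "Group A – active photobiomodulation(n = 15); Group B – sham photobiomodulation(n = 15").
- The abstract gives the order of events: "After the evaluations, the participants will be randomized into 2 groups".

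Two groups and two times imply a group-by-time layout. Section 2.12 itself names neither the factors, nor the error structure, nor the term that carries the treatment comparison, and it does not mention the baseline value.

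**The concern.** A group-by-time ANOVA has a group term, a time term and an interaction, and they answer different questions. The phrase in section 2.12 can be taken to mean the group main effect. That term averages the two occasions. Children are evaluated before they are randomised, so the expected group difference at baseline is zero and the average is diluted.

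A second problem arises if the software is run without declaring time as repeated. The 60 readings from 30 children are then treated as independent. That understates the error of the group term and overstates the error of the interaction.

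With 15 children per arm, the choice of term decides how much of a real effect the trial can detect. A choice left open can also be made after the results are known.

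**Working it through.** **Inputs from the protocol article.** n = 15 per arm (section 2.10), two measurements per child (section 2.4), significance level 5% (section 2.12), randomisation after the first evaluation (abstract). The article gives no power, effect size, SD or sample-size derivation, so there is no stated figure to reproduce.

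**Assumptions.** Bivariate normal data, equal SD σ = 1 at both times, pre/post correlation ρ = 0.3, 0.5 or 0.7, true effect δ = 0 or 1 SD at the last session, two-sided 5% tests.

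**Step 1: what each term estimates.**

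- Group main effect: (0 + δ)/2 = δ/2. For δ = 1 the simulated mean is 0.50. This depends on neither ρ nor σ, and it also holds in a repeated-measures ANOVA.
- Group-by-time interaction (difference in change): δ − 0 = δ.
- Last-session contrast: δ.
- ANCOVA on baseline: δ.

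**Step 2: variances.** With 2/n = 2/15 = 0.1333:

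- Group term: true (2/n)(1+ρ)/2; an ordinary ANOVA assumes (2/n)/2. Ratio 1+ρ, so the test is anti-conservative.
- Interaction: true (2/n)·2(1−ρ); an ordinary ANOVA assumes (2/n)·2. Ratio 1−ρ, so the test is conservative.
- Last-session contrast: 2/n.
- ANCOVA: about (2/n)(1−ρ²).

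The ANCOVA variance is (1−ρ²)/[2(1−ρ)] = (1+ρ)/2 of the interaction variance: 0.65, 0.75 and 0.85 at the three correlations. It is 1−ρ² of the last-session variance: 0.91, 0.75 and 0.51.

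**Step 3: simulated type I error (nominal 5%).**

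| Analysis | ρ = 0.3 | 0.5 | 0.7 |
|---|---|---|---|
| Ordinary ANOVA, group term | 8.3% | 10.7% | 13.1% |
| Ordinary ANOVA, interaction | 2.2% | 0.7% | 0.1% |
| Last-session contrast, pooled ordinary error | 5.0% | 5.3% | 5.2% |
| Repeated-measures group term | 4.9% | 5.0% | 5.0% |
| Repeated-measures interaction | 4.8% | 5.0% | 4.9% |
| ANCOVA | 4.9% | 5.1% | 4.8% |

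**Step 4: simulated power for δ = 1 SD.**

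| Analysis | ρ = 0.3 | 0.5 | 0.7 |
|---|---|---|---|
| Repeated-measures group term | 37% | 33% | 30% |
| Repeated-measures interaction | 61% | 75% | 93% |
| Last-session contrast | 77% | 77% | 77% |
| ANCOVA on baseline | 77% | 85% | 95% |

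The simulations used 20,000 or 40,000 trials per setting.

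**Step 5: check by hand at ρ = 0.5, δ = 1.**

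- Group term: 0.5/√(0.1333 × 0.75) = 0.5/0.316 = 1.58.
- Interaction: 1/√(0.1333 × 2 × 0.5) = 1/0.365 = 2.74.
- Last-session contrast: 1/√0.1333 = 2.74.
- ANCOVA: 1/√(0.1333 × 0.75) = 1/0.316 = 3.16.

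The ordering agrees with the simulated power.

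**The case against.** The strongest reply is that section 2.12 never says the group main effect will be tested, nor that the readings will be treated as independent. An aim framed as before and after treatment points to the interaction at least as readily. A contrast at the last session is also, literally, a between-group comparison. Both estimate the full effect with type I error near 5%. The last-session contrast does so even with the pooled error of an ordinary ANOVA. The article is a condensed text, and a full protocol or SAP may name the term and the error structure. Choosing ANCOVA over a valid interaction is then a matter of efficiency.

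Most of this stands. A reader might infer that the trial, if run as written, will halve its effect, inflate its type I error and probably miss a real benefit. The document does not support that:

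- Halving requires the main effect to be the test. The inflated error requires, in addition, an ordinary analysis.
- These harms do not all fall on one analysis. The 30% to 37% power belongs to the repeated-measures group term, whose type I error is correct. The ordinary group term has inflated error and power of about 48%.
- On the valid readings, a 1 SD effect is detected with 61% to 93% power (interaction) or 77% (last-session contrast).

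A reader might also infer that leaving out age is a fault. The article gives "Four to seventeenyears of age" only as an eligibility range. The ANCOVA simulated here has 30 − 3 = 27 residual degrees of freedom, that is, baseline alone, so nothing in this check supports an age term.

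What the objection does not remove is that section 2.12 names a specific method, and a better one is available from data already collected.

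**Conclusion.** The point holds as an improvement that costs nothing. It does not show an error that must be corrected. The sentence admits both invalid and valid analyses. Only the halving of the main effect is free of numerical assumptions; the type I error and power figures rest on the assumed normality, equal SDs, correlations and 1 SD effect, none of which the article gives.

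The gain from ANCOVA varies. Against the interaction it is 16 points of power at ρ = 0.3 (77 − 61), 10 at 0.5 (85 − 75) and 2 at 0.7 (95 − 93). Against the last-session contrast it is 0, 8 and 18 points. So ANCOVA is never behind in this range, and the analyst need not guess the correlation to choose well. Below the range it can cost a little: at zero correlation its simulated power was 73.5%, against 75.1% for a t test on last-session values.

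**What to change.** Replace the two-way ANOVA sentence in section 2.12, and its counterpart in the abstract, with wording such as:

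> For each continuous outcome (salivary cortisol, salivary dopamine and the EMG measures), last-session values will be compared between the randomised groups by analysis of covariance, with the baseline value of the same outcome as covariate. The treatment effect is the adjusted mean difference, reported with its 95% confidence interval. Group and time main effects from a two-way ANOVA will not be taken as evidence of efficacy.

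Age may be added as a further pre-specified covariate if the investigators expect it to predict the outcome, but that is optional. The four-category BiteStrip score (section 2.8) falls outside this model and should be given an ordinal method.

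If the two-way ANOVA is kept, the minimum clarification is to name group and time as the factors, declare time as repeated within child, and state that the group-by-time interaction tests treatment.

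The cost is a short change to the text and a standard regression routine. It needs no new measurements or participants and should be made before outcome data are seen.

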## Discussion

3

The main objective of the study was to evaluate low intensity laser therapy administered to the use of acupuncture points in children with DS and bruxism. We hope that treatment with acupuncture points will be promising to improve bruxism symptoms in these children and cause a decrease in cortisol levels.
